## Discussion

This study will make a unique contribution to the research literature by providing one of the first longitudinal assessments of a large extracurricular PA intervention designed specifically for adolescent girls, satisfying the important knowledge gap concerning large-scale evaluations of girl-only interventions. It will document its impact on PA levels, which is of crucial importance considering the disengagement from PA participation among this population. It will also be the first study to document the impact on other outcomes such as health, lifestyle and psychosocial indicators (Table 1). To our knowledge, this study will be the first to document the impact of a girl-only PA intervention on perceived body image among girls. This will certainly help better understand the global impact of such interventions. Results will also contribute to increasing the quality and effectiveness of the FitSpirit approach and other girl-only PA interventions. Even though it is not the focus of this intervention, we will also document the impact of such an innovative girl-only approach on obesity prevention.

This study presents many strengths. First, the protocol development process included a pilot study. In addition, most of the questions in the questionnaire have been validated for the specific population assessed (Table 1). Second, this quasi-experimental longitudinal study collects data in real-life school-settings where leaders are supported through a flexible approach in which they can select various FitSpirit activities that best fit their specific needs and challenges. The high number of participants to be recruited is another strength. Data are collected at the beginning and at the end of each school year, a strategic positioning given that the intervention is school-based. Furthermore, the collaborative work of the co-investigators that come from different backgrounds and include various expertise allows this study to assess a broad range of outcomes. The quasi-experimental design of this study comes with some limitations, such as the absence of a control group. In this regard, the co-investigators consider the possibility to compare the results with those collected by large national and provincial surveys, especially since national and provincial questionnaires are used with FitSpirit. The use of self-reported measures could also lead to some biases, such as the social desirability bias. Participation bias cannot be excluded also. One could think that only the most motivated participants would fill the questionnaires. In addition, because each school decides who participate in the FitSpirit activities, it cannot be excluded that in some rare circumstances some schools allow only a specific subgroup of girls to join the program and this subgroup may not represent the general population of adolescent girls.

By documenting the global impact of a holistic school-based girl-only intervention, this study could improve the quality and effectiveness of interventions aimed at promoting PA among girls.

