### Design of the FitSpirit approach

FitSpirit partners with schools to provide activities that get young girls moving and keep them physically active over the long term. It offers tools and services within a holistic approach based on flexible, individualized support to help schools engage girls through girl-only activities tailored to their challenges and their preferences. Non-competitive group activities are planned, organized and led by a member of the school staff, the school program leader, with the support from a regional coordinator. The physical and health education teacher, or any other school employee, can become the FitSpirit school leader. FitSpirit activities can run during the entire school year, with most schools organizing activities only between February and May and for a minimum of 8 weeks (unpublished data). For example, only 67 of the 285 partner schools registered in the school year 2018–2019 have organized FitSpirit activities during fall. In addition, during this same school year, an average of 19 activities have been organized by the partner schools.

FitSpirit offers its support through several services, but mainly the ones listed below. Each partner school decides the extent to which they use and exploit these every year and this information is collected by FitSprit in order to conduct a process evaluation.

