FitSpirit appreciation (secondary outcomes)	• Reasons for participation (in-house questionnaire) • Words associated with FitSpirit (in-house questionnaire) • Participation level (in-house questionnaire) • Satisfaction level (in-house questionnaire) • Injuries (in-house questionnaire)

*PA* Physical activity

**Table 2 Tab2:** Questions evaluating physical activity levels

Questions	
• Over a typical or usual week, on how many days are you physically active for a total of at least 60 min in total per day? Consider only the activities that made you breathe harder and sweat at least a little. ○ None (zero days) ○ 1 day ○ 2 or 3 days ○ 4 to 6 days ○ Everyday	
• In the last 7 days, how long did you use active forms of transportation to get around, like walking to school or cycling to get to work, the shopping center or a friend’s place? (Enter hours AND minutes. You can enter 0 h and 0 min if you have not used active modes of transportation.)	
• In the last 7 days, how long did you do physical activity in your leisure time including exercising, playing an organized or non-organized sport or playing with your friends? (Enter hours AND minutes. You can enter 0 h and 0 min if you have not been active during your leisure time.)	

Data are collected at the beginning and at the end of each school year. Study participants are invited via their personal email address provided at registration to complete the online questionnaire. The end of year questionnaire is also sent to study participants who dropped out from FitSpirit. The longitudinal design of the study will allow the research group to perform an assessment over a prolonged period of time. It will also allow for an evaluation of the persistence of the effects of the program over the summer school break.

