### Trial status

This article presents the protocol as last approved on May 15, 2019. The recruitment began on February 2018 and will be completed at the end of 2022.

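### A start-to-end-of-year change in PA cannot separate season and current FitSpirit sessions from lasting behaviour change, yet the article lists this timing only as a strength

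*Protocol article*

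**What the plan says.** All places are in the protocol article.

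- **Timing of measurement.** Data collection sets two waves per school year, one at its start and one at its end. The Discussion lists this among the strengths: "Data are collected at the beginning and at the end of each school year, a strategic positioning given that the intervention is school-based".
- **Timing of delivery.** Design of the FitSpirit approach: activities can run all year, "with most schools organizing activities only between February and May and for a minimum of 8 weeks". For one school year it reports that "only 67 of the 285 partner schools registered in the school year 2018–2019 have organized FitSpirit activities during fall", with an average of 19 activities organised by the partner schools.
- **Recall period (Table 2).** The leisure item begins "In the last 7 days, how long did you do physical activity in your leisure time", and the active-transport item has the same 7-day window. The item on days with 60 minutes of PA asks about a usual week.
- **Analysis.** Statistical analyses uses the yearly activity count and the years in the programme as independent variables. Length of intervention and baseline habits are examples of covariates. Longitudinal analyses address change in PA, but no pair of time points is named.
- **Limitations.** The Discussion names the lack of a control group, self-report, participation bias and school-level selection. It does not name season.
- **Entry.** Trial status: "The recruitment began on February 2018".

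**The concern.** For most schools, the interval between the two yearly questionnaires opens months before any FitSpirit activity and closes at or near the end of delivery. Active transport and leisure activity can plausibly vary with season. If the end-of-year questionnaire falls while activities are running, minutes spent in FitSpirit sessions can also be reported as PA. Without a control group, nothing in the start-to-end-of-year change separates these two components from a change in what girls do on their own.

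This matters because the programme's declared aim is to keep girls active over the long term. A rise produced by season, or by sessions that are about to stop, would look the same as success. Calling the timing a strength invites that reading.

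**Working it through.** **1. How many schools have a gap between the first questionnaire and delivery?** Input: 67 of 285 partner schools with fall activity (Design of the FitSpirit approach).

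- 67/285 = 23.5% with some fall activity.
- (285 − 67)/285 = 218/285 = 76.5% with none.

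The article's statement about most schools is supported by its own count.

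**2. How much session time could enter a 7-day recall?** Inputs: an average of 19 activities per school year and an 8-week minimum (same section). The upper delivery length of 16 weeks is my assumption for a February-to-May window.

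- 19/16 = 1.2 activities per week.
- 19/8 = 2.4 activities per week.
- If delivery ended before the 7-day window: 0.

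The possible direct contribution therefore runs from none to roughly 1–2 sessions a week. The top value pairs an average count with the minimum duration and assumes full attendance, so it is a ceiling. The article gives no session length, so no figure in minutes follows.

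**3. Does the planned size help?** The article gives no power calculation to reproduce. The 15,000 in Sample size determination is the number of potential participants. I asked how often a shift caused by season alone would be significant at two-sided 0.05. The article gives no size for a seasonal shift, so the shifts below are assumed.

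*Binary outcome.* The starting value is 14%, the Background figure for girls, read here as the share meeting the recommendation. With an unpaired approximation, power = Φ(d/√[(p₁q₁ + p₂q₂)/N] − 1.96). For N = 15,000 and d = 0.01: √[(0.1204 + 0.1275)/15,000] = 0.00407, then 0.01/0.00407 − 1.96 = 0.50, and Φ(0.50) = 0.69.

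| Seasonal shift | N = 15,000 per time point | N = 3,000 per time point |
|---|---|---|
| 1 point | 0.69 | 0.20 |
| 2 points | 0.998 | 0.58 |
| 3 points | about 1.00 | 0.90 |

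*Continuous outcome, paired.* With an assumed within-girl correlation of 0.5, the SD of the difference is SD × √[2(1 − 0.5)] = SD.

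- Smallest shift detectable with 80% power: (1.960 + 0.842)/√15,000 = 0.023 SD.
- A shift of 0.03 SD is significant with probability Φ(0.03 × √15,000 − 1.96) = 0.96.

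These figures treat girls as independent and assume that all 15,000 respond. Clustering by school and non-response would lower them. A large sample makes a small seasonal shift significant; it does not remove it.

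**The case against.** The strongest reply is that the article does not fix start-to-end-of-year as the primary contrast. It follows the same girls each year to May 2022, whether or not they stay in FitSpirit. It plans to look at persistence over the summer break. Its exposure variables compare girls measured in the same season, so a shared seasonal shift partly cancels. The covariates are given only as examples, and the rest may sit in a fuller plan.

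Much of this stands. A reader might infer that the design captures season and sessions *instead of* lasting change. The documents do not support that: a lasting component may be present but cannot be isolated from the within-year change, and the yearly repeats already allow same-season comparisons. A reader might also put a figure in minutes on the session part. That needs a session length, full attendance and activities still running, and the article gives none of these; the listed services also include motivational talks, so not every activity need be exercise. Nor can one say that the first entrants answered in winter. Trial status gives the start of recruitment, not the questionnaire date. Autumn and May as questionnaire months are likewise inferences, because the timeline figure is not shown.

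The reply does not remove the core point. The summer comparison runs from the end of one school year to the start of the next, so it too crosses seasons and moves from during or just after delivery to mostly before it. Activity dose is chosen by schools and girls, and more activities can also mean more session minutes in the recall. The timing is presented only as a strength, whatever a fuller plan contains.

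**Conclusion.** The concern holds in a limited form. With no control group, two waves per school year and delivery mostly from February to May, the start-to-end-of-year change in PA is confounded by season and by current session time. The two 7-day minutes items are most exposed and the usual-week item less so. The size of the bias is unknown. The direct session part lies between zero and roughly 1–2 sessions a week under the assumed 8–16 weeks of delivery, and the article gives no figure for the seasonal part. At the planned size, even a very small shift (about 0.023 SD, under the stated assumptions) would probably be declared significant. The conclusion does not depend on the exact questionnaire months. It requires only that the two waves fall in different seasons and that the second lies in or near the delivery period.

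**What to change.** 1. State that the within-year change alone will not be interpreted as the programme's effect on PA.
2. Report same-season within-girl contrasts beside it: end-of-year to end-of-year first, because the end-of-year questionnaire is the one described as going to girls who have left FitSpirit, with start-to-start as a sensitivity analysis. State two limits. Ageing remains confounded with time, because every pair spans about a year. Session time is balanced only for girls active in the programme in both years.
3. Use the existing Table 1 item that distinguishes PA at school from PA elsewhere to report outside-school PA separately.
4. Include season or date of questionnaire completion in the models where available. The article does not say whether the research team receives dates.
5. Analyse separately girls whose first questionnaire was not at the start of a school year, possibly those recruited from February 2018.
6. Add the timing to the limitations in the Discussion.

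The cost is modest: no new questionnaire item or wave, mainly analysis wording and a little more analysis. The price is fewer pairs, since same-season contrasts need a further year of follow-up.

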### Trial status

This article presents the protocol as last approved on May 15, 2019. The recruitment began on February 2018 and will be completed at the end of 2022.

## Data Availability

Data sharing is limited to the study research team and all analyses will be carried out internally. Each paper or abstract must be submitted to the Subcommittee for review of its appropriateness and scientific merit prior to submission. The Subcommittee may recommend changes to the authors.

## Abbreviation

PA: physical activity
